# INTRODUCTION

**Purpose of statistical analysis plan**

The purpose of this document is to provide details of the statistical analyses and presentation of results to be reported within the principal paper(s) of the SWAP trial. Subsequent papers of a more exploratory nature (including those involving baseline data only) will not be bound by this strategy but will be expected to follow the broad principles laid down in it. Any exploratory, post hoc or unplanned analyses will be clearly identified in the respective study analysis report.

The structure and content of this document provides sufficient detail to meet the requirements identified by the International Conference on Harmonisation (ICH) and the PCTU SOP (PCTU/07).

**Members of the writing committee**

[name] and [name] were primarily responsible for writing the Statistical Analysis Plan, with input from other members of the Trial Management Group.

This document has been finalised before any members of the Trial Management Group had access to the trial data, or were unblinded to trial results.

**Summary**

The SWAP trial aims to determine whether a group-based weight management programme (Weight Action Programme; WAP) targeting underprivileged groups is superior to ‘best practice’ weight management that is provided in primary care by practice nurses.

**Background to the Weight Action Programme**
Weight Action Programme (WAP) is a multi-modal health behaviour modification intervention developed at the Wolfson Institute of Preventive Medicine via extensive client feedback and piloting with underprivileged groups since 2002. The programme is a multi-component service that aims to provide participants with tools to lose weight and maintain a long-term healthy lifestyle. The contents include the standard elements of cognitive behavioural interventions, dietary advice, self-monitoring, information on healthy cooking and eating and caloric content of food, cue management, provision of opportunities for exercise and close monitoring of exercise levels, and a range of concrete and verifiable tasks agreed individually with each participant. Participants are asked to wear a pedometer in order to record daily number of steps at baseline. Throughout the course, individual pedometer step targets are gradually increased until an optimal sustainable level is reached. An innovative feature of the programme consists of the use of group-oriented interventions aiming to increase participant retention, involvement and adherence to weekly tasks. This also makes the programme more cost-effective. The focus of the WAP course is to help participants to maintain a healthy lifestyle after the programme finishes.

The programme has been developed to cater specifically for underprivileged groups including ethnic minorities. Where information is imparted, it is mostly in pictorial and easily understandable format.

WAP has been evaluated in two pilot studies of 162 overweight adults (mean BMI of 35 kg/m2) from multi-ethnic areas of high deprivation.[1] The average weight loss was 2.8kg at end of treatment and 4.5kg at 3-month follow-up (with 24% participants attending follow-up losing 5% or more of their body weight). Limited promotion via GP practices and local adverts generated a large volume of interest. The client retention was at least as good as in comparable programs conducted in research settings with more traditional clients (59% completed the 6-week treatment) and the program received very high approval ratings. Clients also demonstrated significant improvements in knowledge of healthy eating, and in their exercise levels as measured by pedometer monitoring. Clients considered the group support essential in helping them to stick to their tasks and to lose weight.[1] WAP also includes information on orlistat.

We recruited from and conducted the interventions in two GP practices, one in the London borough of Hackney and the other in Tower Hamlets. Both boroughs have a high level of deprivation.

**Changes from planned analysis in the protocol**

In the original trial protocol we specified we would use a baseline-observation-carried-forward approach (BOCF) for dealing with patients with missing weight data during follow-up. This approach assumes that all those who were lost to follow-up returned to their exact baseline weight. Whilst this approach has been commonly used in other randomised controlled trials, it is problematic because it will provide biased estimates of the treatment effect when this assumption is incorrect (i.e. when participants do not return to their exact baseline weight when they fail to show up to their 6 or 12 month appointment). In addition, BOCF will often lead to an inflated type I error (false-positive) rate as it tends to underestimate the standard error for the treatment effect (due to ignoring the within-patient variability in weight when imputing using BOCF).

We have therefore decided to use a mixed-effects linear regression model for the primary analysis. This analysis method provides unbiased estimates of treatment effect and correct type I error rates provided the data is missing-at-random (MAR); that is, that the probability that a participant is lost to follow-up depends on either their previous weight measurements (e.g. their weight at baseline and 6 months if they are lost-to-follow-up at 12 months), and baseline patient characteristics (See section 5 for variables we are adjusting for). [2]

This strategy of analysis has been widely recommended in the presence of missing outcome data. We made the decision to change analysis methods before we had any access to the trial data, or ongoing trial results, and therefore there is no risk of bias associated with this decision.

**Changes from SAP version 1.0**
Version 2.0 of the SAP specifies that all linear mixed-effects models will employ the Kenward-Roger degree-of-freedom correction. This decision was undertaken prior to any member of the trial team having access to unblinded data, or ongoing trial results.

1. **STUDY OBJECTIVES AND ENDPOINTS**

**Study objectives**

Primary objectives

To determine if WAP can generate a better sustained weight loss over 12 months in overweight adults than best-practice intervention that is routinely provided by nurses in general practice.

Secondary objectives

1. To determine the cost-effectiveness (in terms of costs of interventions and QALYs derived from the EQ-5D) of the two interventions

**Outcome measures**

Primary outcomes

The primary outcome measure is the change in weight (in kg) at 12 months post-randomisation.

Secondary outcomes

- Change in weight (in kg) at 1, 2, and 6 months post-randomisation.
- Change in BMI at 1, 2, 6 and 12 months post-randomisation. BMI is calculated as weight (in kg) divided by the square of height (in metres). The height measured at screening will be used for each follow-up assessment.
- Change in waist circumference (in cm) at 2, 6 and 12 months post-randomisation.
- Change in systolic blood pressure (mmHg) at 2, 6 and 12 months post-randomisation.
- Change in diastolic blood pressure (mmHg) at 2, 6 and 12 months post-randomisation.
- Change in the Food Craving Inventory score (Frequency domain) at 1, 2, 6, and 12 months post-randomisation.
- Change in the Food Craving Inventory score (Strength domain) at 1, 2, 6, and 12 months post-randomisation.
- Change in Food Knowledge Assessment Questionnaire score at 2, 6, and 12 months post-randomisation.
- Change in the Three Factor Eating Questionnaire score (Cognitive Restraint domain) at 2, 6, and 12 months post-randomisation.
- Change in the Three Factor Eating Questionnaire score (Uncontrolled Eating domain) at 2, 6, and 12 months post-randomisation.
- Change in the Three Factor Eating Questionnaire score (Emotional Eating domain) at 2, 6, and 12 months post-randomisation.
- Change in the International Physical Activity Questionnaire (IPAQ) score (MET-minutes/week domain) at 2, 6, and 12 months post-randomisation.
- Change in the International Physical Activity Questionnaire (IPAQ) score (Sitting domain) at 2, 6, and 12 months post-randomisation.
- Proportion of participants losing 5% of body weight at 2, 6, and 12 months post-randomisation.
- Proportion of participants losing 10% of body weight at 2, 6, and 12 months post-randomisation.

Scoring details for the Food Craving Inventory, the Food Knowledge Assessment Questionnaire, the Three Factor Eating Questionnaire, and the International Physical Activity Questionnaire are available in Appendix 2.

Weight, BMI, waist and blood pressure outcomes were measured by researchers who were blind to treatment arm. These researchers were affiliated with the trial team, but were involved only in collecting outcomes during follow-up, and had no role in providing the intervention, and no contact with patients other than whilst collecting follow-up measurements.

1. **STUDY METHODS**

**Overall study design and plan**

Target for randomisation: 220 intervention and 110 control participants

Date of first randomisation: 27/09/2012

Date of last randomisation: 30/01/2014

Trial design: Individually randomised, parallel group

Who is blinded: Researchers affiliated with the study team conducting measurements at 6 and 12-month follow-up. Patients and those delivering the intervention are aware of the patient’s treatment allocation.

Randomised Interventions: Intervention (WAP) vs. control (Nurse counselling)

Allocation ratio: 2:1

**Selection of study population**

The study population was selected from people responding to letters and text messages sent from their GP surgery, posters in surgery waiting areas, direct referrals from GP staff and advertisements in local papers.

Participants were eligible to take part if they were age 18 years and older, wanted to lose weight, and had a BMI of 30 kg/m^2^ or over, or a BMI of 28 kg/m^2^ or over with co-morbidities.

Participants were excluded from participating if they could not read, write, or speak English, had a BMI over 45 kg/m2, had lost more than 5% of their body weight in the previous 6 months, were pregnant, currently taking psychiatric medications, were not registered with a GP, or currently involved in another research project.

**Method of treatment assignment and randomisation**

Participants were randomly allocated to the two treatment arms in a 2:1 ratio (intervention:control) by means of an independent web-based randomisation service. Allocation was via random permuted blocks stratified by GP Practice (Lawson vs. Barkantine) with randomly varying block sizes of 18, 21, and 24.

Randomisation was undertaken within each GP practice. Study staff accessed the web-based randomisation programme developed by the Sheffield Clinical Trials Unit, University of Sheffield and entered the participant ID number into the programme. No other information was entered. The allocation was immediately provided by the programme and participants were given instruction on what to do for the next sessions. Neither participant nor study staff were blind to the allocation after this point.

**Treatment masking (Blinding)**

Participants and study staff providing the interventions were not blinded. However the study staff collecting the measurements at 6 and 12-month follow-up (the primary endpoint) were blinded to allocation.

The statistician (and all other staff who have access to outcome data) remained blinded until the database was finalised and Statistical Analysis Plan is signed off.

**Sample size determination**

A clinically significant effect can be achieved with 3-5 kg weight loss in obese people.[3] We assumed that WAP would increase weight loss by 2.6kg compared with usual care (WAP 3kg vs. usual care 0.4kg) for participants available for follow-up at one year, and that there would be no difference in weight loss between treatment groups for participants not available for follow-up. Assuming that 50% of participants in both treatment groups were available for follow-up at one year, the difference in weight loss between groups would be 1.3kg (WAP 1.5kg vs. usual care 0.2kg). Assuming a standard deviation of 3 in both treatment groups, and a 5% two-sided significance level, we would require 112 participants in each group to detect this mean difference with 90% power. Our estimate of 50% loss to follow-up is conservative and based on international experience in this field and existing data from similar underprivileged and highly mobile populations and interventions.

To account for potential clustering effects due to group treatment in the intervention arm, assuming a mean cluster size of 18 and an intra-cluster correlation coefficient of 0.05, a total of 208 individuals will be required in the intervention arm. The same power can be achieved with 108 in the control arm and 216 in the intervention arm which we have increased to 110 in the control arm and 220 in the intervention arm to give an allocation ratio between the two arms (2:1) which can be expressed in whole numbers. Thus we require a total of 330 individuals for the entire study

1. **DATA COLLECTION**

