**General analysis principles**

The main analysis for each outcome will use intention-to-treat (ITT) principles, meaning that all participants with a recorded outcome will be included in the analysis, and will be analysed according to the treatment group to which they were randomised. More information on which participants will be included in each analysis is available in the section below. All p-values will be two sided, and the significance level is set at 5%.

Analyses for all outcomes will be presented as:

- The number of participants included in the analysis, by treatment group;
- A summary measure of the outcome, by treatment group (e.g. mean (SD) for continuous outcomes, number (%) for binary outcomes);
- A treatment effect, with a 95% confidence interval;
- A two-sided p-value.

All analyses will account for clustering by group in the intervention arm, and clustering by nurse in the control arm. Each patient will be defined as belonging to a cluster, defined by which group they belonged to if they were in the intervention arm, and which nurse they were treated by if they were in the control arm. This variable will be included as a random intercept in a mixed-effects regression model. This analysis assumes the intraclass correlation coefficient is the same between groups in the intervention arm as it is between nurses in the control arm. The Kenward-Roger degree-of-freedom correction will be employed for all linear mixed-effects models.

All analyses will adjust for baseline weight, age, gender, ethnicity (White British, White other, Black, Asian, Mixed, or other), smoking status (smoker vs. non-smoker) and GP practice (Lawson vs. Barkantine) as covariates in a regression model. Outcomes which are measured at baseline will also be adjusted for the value of the outcome at baseline (this includes weight, BMI, waist circumference, systolic and diastolic blood pressure, Food Craving Inventory, Food Knowledge Assessment, Three Factor Eating Questionnaire, and IPAQ). Continuous covariates (baseline weight, age) will be assumed to have a linear association with outcome. Binary and categorical covariates (gender, ethnicity, smoking status, and GP practice) will be included in the regression model using indicator (dummy) variables. Missing baseline data will be accounted for using mean imputation.

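### The stated 90% power for 1.3 kg allows for clustering in the WAP arm only, whereas the analysis also clusters controls by nurse with the same ICC

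*SAP*

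**What the plan says.** **Planning (SAP, Sample size determination).** The unclustered step takes a 1.3 kg difference, two-sided 5% significance and the following: "Assuming a standard deviation of 3 in both treatment groups". It concludes that "we would require 112 participants in each group to detect this mean difference with 90% power". The clustering step is limited to one arm: "To account for potential clustering effects due to group treatment in the intervention arm, assuming a mean cluster size of 18", with an ICC of 0.05, which raises the WAP arm to 208. For 2:1 allocation the section then says: "The same power can be achieved with 108 in the control arm and 216 in the intervention arm". These become 110 and 220. No cluster size, ICC or design effect is given for controls.

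**Analysis (SAP, General analysis principles).** "All analyses will account for clustering by group in the intervention arm, and clustering by nurse in the control arm". Group or nurse enters as one random intercept, and the SAP adds: "This analysis assumes the intraclass correlation coefficient is the same between groups in the intervention arm" as between control-arm nurses. The section Analysis of primary outcome repeats this intercept for the primary model. Version 2.0 adds the Kenward-Roger correction to all linear mixed models.

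**Not stated.** The number of nurses is a blank cell in Table 2. The SAP does say that recruitment and delivery took place in two GP practices.

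**The concern.** The two parts of the SAP assume different things about the control arm. Planning treats controls as independent. The analysis treats controls who share a nurse as correlated, to the same degree as WAP participants who share a group. A positive ICC with more than one control per nurse cannot give a design effect of 1, so the power statement and the analysis model cannot both be right as written.

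What is at stake is the reading of the result. If the principal paper repeats 90% power for 1.3 kg, a null finding will look more conclusive than the specified analysis supports. The effect estimate itself is not biased by this.

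**Working it through.** **Inputs from the SAP:** difference 1.3 kg; SD 3; two-sided 5%; WAP cluster size 18; ICC 0.05; 220 WAP and 110 control. **Assumption:** the number of nurses k, with controls spread evenly.

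**Step 1: reproduce the plan.**
- Unclustered: 2 × (1.96 + 1.2816)² × 3² / 1.3² = 111.9, so 112 per arm.
- WAP design effect: 1 + (18 − 1) × 0.05 = 1.85, and 112 × 1.85 = 207.2, so 208.
- SE = 3 × √(1.85/n_WAP + DE_control/n_control); power = Φ(1.3/SE − 1.96).
- With DE_control = 1.00: 216/108 gives SE 0.4005 and power 90.1%; 220/110 gives SE 0.3969 and power 90.6%.

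The plan's arithmetic is therefore correct, on a control design effect of 1.00.

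**Step 2: apply the SAP's equal-ICC assumption to controls.** DE_control = 1 + (110/k − 1) × 0.05, at 220/110. The t column uses a noncentral t with df = k + 220/18 − 2 (clusters minus 2), a rough stand-in for Kenward-Roger. The detectable difference at 90% power is (1.96 + 1.2816) × SE.

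| Nurses (assumed) | Controls per nurse | DE_control | SE | Power, normal | Power, t | Detectable, kg (normal) |
|---|---|---|---|---|---|---|
| 2 | 55 | 3.70 | 0.615 | 56% | 49% | 1.99 |
| 4 | 27.5 | 2.33 | 0.516 | 71% | 65% | 1.67 |
| 6 | 18.3 | 1.87 | 0.478 | 78% | 72% | 1.55 |
| 8 | 13.8 | 1.64 | 0.458 | 81% | 77% | 1.48 |
| 10 | 11 | 1.50 | 0.445 | 83% | 79% | 1.44 |
| 20 | 5.5 | 1.23 | 0.419 | 87% | 85% | 1.36 |

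With normal quantiles, power is already 89.9% at 2 controls per nurse (55 nurses). It drops below 88% at about 4.75 controls per nurse.

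**Step 3: vary the ICC (normal quantiles).**
- ICC 0.02 in both arms: about 78, 86, 89 and 91% for 2, 4, 6 and 8 nurses.
- ICC 0.02 in the control arm only, WAP kept at 0.05: about 75, 83, 85 and 87%. This departs from the SAP's equal-ICC assumption.

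**Step 4: check the effect and the follow-up assumption.** The 1.3 kg is 2.6 kg halved for 50% loss to follow-up: 3 and 0.4 kg become 1.5 and 0.2 kg, which amounts to zero change in those lost. That fits baseline-observation-carried-forward with all 330 participants contributing, an approach that the SAP drops for a missing-at-random mixed model. With only half observed (110/55, cluster sizes halved, ICC 0.05 in both arms, earlier visits ignored, normal quantiles):
- If the model targets 2.6 kg with SD 3, power is 96% with 2 nurses and 99% with 4.
- If it targets 2.6 kg with SD 3.67, power is 86% and 93%. An SD of 3.67 among those observed in WAP gives 3 overall once half are set to zero: 0.5 × 13.5 + 0.25 × 3² = 9, and √13.5 = 3.67.
- If it targets 1.3 kg with SD 3, power is 46% with 2 nurses and 56% with 4.

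**The case against.** **The sums are right.** True: every planning figure reproduces. A reader might infer a calculation error, but the fault is a mismatch of assumptions between two sections.

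**The planned analysis might still have 90% power.** This stands. A reader might infer from the table that the current primary analysis is underpowered. The SAP does not support that, because the 1.3 kg belongs to the abandoned analysis, and Step 4 shows power on either side of 90% depending on what the mixed model targets. The planning also takes no credit for covariates. If they explained 25% of the variance (an assumption), power for 1.3 kg would be about 83, 88 and 92% with 4, 6 and 10 nurses.

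**The number of nurses and their ICC are unknown.** This stands too, and it is why only a range can be given. The 0.05 was set for group treatment, and its use for nurses rests on the equal-ICC assumption in the analysis section. Few nurses are plausible with two practices, but the SAP does not say so. A reader might also infer that the loss persists whatever the ICC, but with 0.02 in both arms power is about 91% at 8 nurses.

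**Recruitment is over and every effect will have a 95% confidence interval.** This limits the consequence, since the interval reflects the nurse variance. It does not make the stated power agree with the model.

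**Conclusion.** The point holds in a limited form. The 90% for 1.3 kg rests on no clustering among controls, while the same SAP models nurse clustering with an ICC equal to that of the groups. On the planning inputs (1.3 kg, SD 3, ICC 0.05, 220/110, all 330 contributing), power falls short unless nurses treat very few controls each. It is about 56 to 87% for 2 to 20 nurses with normal quantiles, and about 49 to 85% with the approximate t reference. The size depends on an unstated number of nurses and on an ICC carried over from group treatment, and it ignores any gain from covariates. Nothing here shows what power the missing-at-random primary model actually has.

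**What to change.** In Sample size determination, restate the power and the detectable difference for 220/110 with a design effect in both arms, using the actual number of nurses and a t reference. Say which effect (1.3 or 2.6 kg) and which follow-up assumption the figure refers to.

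If the sponsor holds that nurse clustering is nil, as the sample size implies, the SAP should say so, justify it, and use a partially nested model with a cluster effect in the WAP arm only. Giving each arm its own cluster variance would not reconcile the two sections, because it still estimates a nurse variance that planning set to zero.

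The cost is SAP wording and, for the first option, probably a less favourable stated power. No extra participants are needed. The partially nested option carries one risk: if nurses do differ, its standard error will be too small.

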**Baseline**

The following variables were collected at baseline

- ***Demographics:*** includes age, sex, ethnicity, employment, level of education
- ***Health and lifestyle:*** includes smoking status, alcohol consumption, and general health
- ***Weight loss history:*** includes number of past weight-loss attempts, methods used, most weight ever lost, and regular monitoring of weight.
- ***Concurrent medications:*** all current medications are recorded.
- ***Height and weight:*** measured in centimeters and kilograms. BMI calculated from these.
- ***Waist circumference:*** measured in centimetres.
- ***Blood pressure:*** resting blood pressure recorded.

The following validated questionnaires are also administered at baseline:

- International Physical Activity Questionnaire [4]
- Food knowledge assessment
- Food craving inventory [5]
- Three Factor Eating Questionnaire [6]
- EQ-5D
- Use of health services questionnaire

